##### Acceptability of Intervention Measure-4

The Acceptability of Intervention Measure (AIM) is used to determine the extent to which an intervention is perceived to be acceptable by its participants [69]. The AIM has four items rated on a 5-point scale; items are averaged for each scale to yield a total score, ranging from 1 to 5. The AIM has demonstrated strong psychometric properties, including validity, reliability, and responsiveness to change. This measure has been implemented in studies on Kenyan adolescents or those experiencing, or at risk of developing, mental health difficulties [70, 71].

##### Intervention Appropriateness Measure-4

We will administer the four-item Intervention Appropriateness Measure (IAM) to assess whether participants believe the intervention is appropriate [53]. Similar to AIM, IAM has four items rated on a 5-point scale, with items averaged for each scale to yield a total score that ranges from 1 to 5. IAM has also demonstrated strong psychometric properties and has been implemented in studies with Kenyan adolescents and those experiencing, or at risk of developing, mental health difficulties [70, 71].

##### Demographic Questionnaire

The demographic questionnaire asks participants to report their basic demographic information, including their age, year in school, gender, family financial status, religion, county of origin, location of home (e.g., rural, urban), motivation to participate, and the ethnic background (i.e., tribe) they belong to.

##### Program Feedback Scale

The measure includes questions for participants about the interventions they participated in (e.g., which sessions they thought were most helpful) and whether they experienced change on hypothesized mechanisms of change (e.g., if they noticed themselves becoming more aware of their core values and sense of purpose as a result of the intervention). The measure also seeks other suggestions from participants about how the program can be improved for future implementation.

##### Perceived Control Scale for Children

The Perceived Control Scale for Children (PCSC) [72] aims to assess children’s perceived control (i.e., the belief that they are capable of achieving things that they want (or avoiding things they do not) with effort. The original 24-item questionnaire includes subscales reflecting perceived control over academic, social, and behavioral outcomes. A 6-item version of the original scale, devised using factor analysis and graded response modeling, will be used in the study.

##### Secondary Control Scale for Children

The Secondary Control Scale for Children (SCSC) assesses perceptions of secondary control, or one’s perceived ability to adjust oneself to hardships in such a way as to control their subjective emotional impact [73]. A 6-item version of the original 20-item scale, devised using factor analysis and graded response modeling, will be used in the study.

##### Mechanisms of Change

We will also include items designed to measure the extent to which participants have changed their thoughts and actions based on the character strength interventions. For each construct (gratitude, growth, values, and study skills), we will ask participants to complete two items designed to assess the extent to which participants have intentionally thought about the character strength or acted based on the character strength over the past 2 weeks (the items can be found in the supplemental materials). These items are intended to help us understand if the interventions produce their intended effect, as well as to understand potential mechanisms of change of each intervention.

##### Qualitative Participant Feedback

As part of the Program Feedback Scale completed post-intervention, every participant will be asked to provide qualitative feedback on their assigned condition including their favorite aspect of the program, what they would change, and any other feedback or comments. Additionally, at the second follow-up point (3-month follow-up), the study team plans to convene focus groups of participants to discuss their feedback on the condition to which they were assigned and any changes in their feelings, thoughts, and behaviors since participating in the program.

##### Group Leader Feedback Questionnaire

The feedback questionnaire asks for feedback from group leaders about the training they have received. There are two anonymous feedback questionnaires that group leaders will fill out; one will be distributed immediately post-training, and the other after the leaders have completed the program. Each questionnaire asks the group leaders to indicate their satisfaction with the training, on a scale of 1 (the training is terrible and makes them feel extremely unprepared) to 7 (the training is fantastic and makes them feel well-prepared to lead the sessions); the second section asks these leaders to circle, from 1 (strongly disagree) to 5 (strongly agree), their thoughts on the quality of the training (e.g., whether the training is taught clearly) and if they become comfortable learning from the Shamiri team (e.g., whether the Shamiri team clearly conveys expectations and respect toward the group leaders during the training). The last section includes several short answer questions that ask these group leaders to give written feedback about the program and suggestions for improvement.

### Participant timeline {13}

School recruitment will begin in May 2021, with participant recruitment then beginning in late May of 2021, and the consenting process occurring in late May of 2021 immediately prior to baseline assessment. Baseline assessment of demographic variables, some of which will be accounted for in randomization, and of primary and some secondary outcomes will be completed immediately after consenting. Within the n1ext week, allocation will occur, and the first intervention sessions will begin in late May or early June. Immediately prior to those sessions, students will complete other baseline measures of remaining secondary outcomes. At the 2-week intervention midpoint in June, participants will complete midpoint measures of primary outcomes and potential intervention mediators (i.e., some secondary outcomes) immediately post-session. At the 4-week intervention endpoint in late June or early July, participants will complete all primary and secondary outcome measures and measures of intervention feedback. Finally, at 1-month follow-up (August), 3-month follow-up (October), 6-month follow-up (January), and 9-month follow-up (March), participants will again complete all measures of primary and secondary outcomes. See Fig. 1 for the SPIRIT diagram depicting the intervention, assessment, and enrollment timeline.

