### Eligibility criteria {10}

Youths will be eligible for inclusion if they are a student in a participating school between the ages of 12 and 21. This will be a universal intervention and participants will not be screened in any way in, so long as they are in Form 2 and Form 3 (second and third years in high school). Participants who fail attention checks during baseline measures will be excluded. No participant who meets these criteria will be excluded for any other reasons other than the capacity of the groups: should more students than we can have in the group be interested in participation, we will randomly select students to join the groups.

The lay providers delivering the intervention will be eligible if they are living near Nairobi, Kenya, if they attended and graduated from a Kenyan high school, and if they are between the ages of 18 and 24. Among those applicants who meet criteria, the study team will conduct interviews to select those who seem to have the strongest counseling skills, commitment to the project, and understanding of the challenges commonly faced by Kenyan high schoolers. Applicants will first be evaluated via a brief written application, then via 30-min interviews including questions about experiences, motivations, and hypothetical scenarios. Full information about the process of interviewing and evaluating lay provider applicants can be found in [35]. Additionally, the study team will prioritize hiring those between 18 and 22. The recruitment and training process for lay providers in this trial will closely resemble that employed in a previous RCT of the Shamiri Intervention [35].

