## Data collection and management

### Plans for assessment and collection of outcomes {18a}

As discussed under {12}, primary outcomes include participants’ severity of youth depression symptoms (as measured by the PHQ-8), levels of anxiety symptoms (GAD-7), academic performance (standardized scores representing students’ mean grades across enrolled subjects), and mental wellbeing (SWEMWBS). Secondary outcomes include participants’ character strengths related to wellbeing (per the EPOCH), perceived meaning and life purpose (PILS-12), gratitude (GQ-6), implicit theories of personality (IPTQ), use of intervention strategies, and personal satisfaction with social support (MSPSS). Measures of intervention acceptability and appropriateness among participants (AIM and IAM, respectively) will also be collected, along with basic demographic information (Demographic Questionnaire). The study team will also elicit program feedback from both study participants and group leaders. Study scales and questionnaires, as well as their reliability and validity, are further detailed under {12}.

Measures of demographic variables and primary outcomes will constitute one baseline data collection form, to be administered and collected by the study team immediately following the consenting/assenting process. Lay providers will then pass out baseline measures of secondary outcomes under supervision from study staff by asking participants to complete a separate questionnaire battery with primary outcomes immediately prior to the first intervention sessions. These same lay providers will administer, under the supervision of study staff, measures of primary outcomes and potential mediators (including some secondary outcomes) at the intervention midpoint, and all primary and secondary outcome measures and intervention feedback measures at the endpoint. Trained supervisors and the Kenyan study PI ([name]) and Co-I ([name]) will ensure data confidentiality and adherence to data collection protocols among lay providers at each of these stages. Supervisors will also collect physical questionnaires immediately from the group leaders, which trained study team members will scan and upload according to the procedures described under {27}.

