## Statistical methods

### Statistical methods for primary and secondary outcomes {20a}

Outcome measures will only be analyzed if they demonstrate internal consistency within the full sample at baseline, defined as an alpha value of .70 or above [75]. For those outcome measures that pass this threshold, all main analyses of primary and secondary outcomes will follow an intent-to-treat approach, meaning that all participants who consent, are randomized into the groups, and complete baseline measures will be included in all analyses (see 20c below for more about plans for handling missing data).

For all analyses of primary and secondary outcomes, we plan to use linear mixed effects models to model time × condition interaction with a random intercept for participant ID to allow for individual variation at baseline. We plan to control for age and sex in all models of primary and secondary outcomes. Age will be included because older adolescents report increased psychosocial stress and thus greater risk of mental illness [3]. Similarly, sex differences in anxiety and depression are widely documented in adolescents including Kenyan adolescents [3, 76]. Additionally, the authors will test more complicated random effects structures which reflect the hierarchical structure of the data, including random effects for groups within group leaders, crossed random effects for schools and group leaders, and for participants in groups. We will also test adding a random slope for participant ID and for school; however, these added random effects may result in overfitting, which would reduce the generalizability of our findings. If this is the case, we will select a more parsimonious model with a simpler random effects structure. These variables (group leader, school, and group) will also be tested as covariates rather than random effects in the model, and final model selection will be done taking into account both overfitting warnings and Akaike Information Criterion (AIC) [77].

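### Some secondary-outcome baselines are taken unblinded after allocation, and the intent-to-treat set depends on completing baseline, so randomised students can be removed for a post-allocation event

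*Protocol article*

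**What the plan says.** **Order of events.** Under Participant timeline {13}, demographics and measures "of primary and some secondary outcomes will be completed immediately after consenting". Then: "Within the n1ext week, allocation will occur, and the first intervention sessions will begin in late May or early June". Immediately before those sessions, "students will complete other baseline measures of remaining secondary outcomes". Sequence generation {16a} says that allocation follows the baseline assessment and does not mention a second part.

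**Content of the two forms.** {13} puts primary and some secondary outcomes on the first form and only the remaining secondary outcomes on the second. Plans for assessment and collection of outcomes {18a} says "Measures of demographic variables and primary outcomes will constitute one baseline data collection form". It then describes the second sitting as baseline measures of secondary outcomes, yet also as "a separate questionnaire battery with primary outcomes immediately prior to the first intervention sessions".

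**Who administers the second form.** {18a} gives this to lay providers, supervised by study staff. Implementation {16c} assigns group leaders to particular groups once the allocation list exists. Who will be blinded {17a} says that participants, lay providers and the staff working with them cannot be blind to condition.

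**Who is analysed.** {18b} keeps students who miss sessions in the study, but excepts the first session because essential baseline data are collected there. It continues grade collection for those who leave or are removed after the first session. {20a} describes an intent-to-treat approach in which "all participants who consent, are randomized into the groups, and complete baseline measures will be included in all analyses".

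**The concern.** A baseline should be fixed before anyone knows the assignment. Here, students who know their group, and may have formed expectations about it, give their starting values on some secondary scales. Three of the secondary measures correspond closely to single arms: the gratitude questionnaire, the implicit personality theory questionnaire and the purpose in life scale. If knowing the arm moves such a score at the second sitting, the shift enters the baseline and distorts change from baseline. It would also enter the exploratory mediator analyses.

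The second problem is the analysis set. If completing baseline includes a form filled in at session 1, membership of the intent-to-treat set depends on attendance after allocation. Attendance can differ by arm, since students know what they have been assigned to. This reaches every outcome, including the primary ones and grades, because a student outside the set is outside it for everything.

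**Working it through.** **1. The sections side by side**

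| Question | {13} | {18a} | {16a} |
|---|---|---|---|
| Primary outcomes before allocation? | Yes | Yes, on the first form | PHQ-8 and GAD-7 must be, as they are stratifiers |
| Any secondary outcomes before allocation? | Some | None listed on the first form | Not stated |
| Primary outcomes repeated after allocation? | No | Yes, as worded | Not stated |
| Any baseline after allocation? | Yes, remaining secondary outcomes | Yes, a separate battery | Implied no |

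All accounts are consistent with a pre-allocation baseline for the primary questionnaires. Baseline grades come from the term before the intervention. {13} and {18a} agree that some secondary baselines follow allocation. They disagree on how many, and on whether primary outcomes are measured a second time.

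**2. Effect of a baseline shift**

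Let d be the shift, in SD, in one arm's post-allocation baseline.

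- *Simple gain score* (the effect sizes in {20a}): the contrast moves by d.
- *Time × condition in a random-intercept model.* Assume linear time in months from baseline, with visits at 0, 0.5, 1, 2, 4, 7 and 10, and complete data. The slope's weight on the baseline visit is (t₀ − t̄)/Σ(t − t̄)².
  - Full follow-up: t̄ = 24.5/7 = 3.5; Σ(t − t̄)² = 170.25 − 7 × 12.25 = 84.5. Over 10 months the shift is 10 × 3.5/84.5 = 0.41d.
  - To the 1-month follow-up (0, 0.5, 1, 2): t̄ = 0.875; Σ(t − t̄)² = 5.25 − 4 × 0.7656 = 2.1875. Over 2 months it is 2 × 0.875/2.1875 = 0.80d.
  - {13} takes only some secondary outcomes at the midpoint. Without that visit the factors rise: 10 × 4/74 = 0.54d (t̄ = 24/6 = 4; 170 − 6 × 16 = 74), and 2 × 1/2 = 1.0d for visits at 0, 1 and 2.

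The document gives no value for d. Assume 0.05 to 0.15 SD, and take the 0.3 SD from Sample size {14} as the yardstick:

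| Estimate | d = 0.05 | d = 0.15 |
|---|---|---|
| Gain score (1.0d) | 0.05/0.3 = 17% | 0.15/0.3 = 50% |
| Slope to 1 month, every visit (0.80d) | 0.04/0.3 = 13% | 0.12/0.3 = 40% |
| Slope over full follow-up, every visit (0.41d) | 0.0207/0.3 = 7% | 0.0621/0.3 = 21% |

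**3. Effect of removing students after allocation**

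The plan's own figures reproduce: 515 × 2.5 = 1287.5, rounded up to 1288; 1288/0.6 = 2146.7, rounded up to 2147 invited. The number randomised is not stated, so take 2147 as an upper bound. If 2%, 5%, 10% or 20% miss session 1 (assumed rates), about 43, 107, 215 or 429 randomised students leave the set.

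If arm A loses a fraction q_A, control loses q_C, and those removed differ from those who stay by δ SD, the contrast is biased by (q_A − q_C) × δ:

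- Equal removal, 5% and 5%: 0.
- 10% against 5%, δ = 0.3 to 0.5: 0.015 to 0.025 SD, or 5 to 8% of 0.3.
- 15% against 5%, same δ: 0.03 to 0.05 SD, or 10 to 17% of 0.3.

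The multiple imputation in {20c} fills gaps for students in the set. It does not restore students whom the set's definition leaves out.

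**The case against.** Much can be said for the plan. The second battery comes before any session content. Students and lay providers are not told the hypotheses, and the control is presented as one of a series of interventions ({17a}). Administrators do not see answers, and students are told so ({17b}); lay providers are not told scores ({27}). These safeguards make a large shift less likely. They do not make the second sitting blind.

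Four stronger readings are tempting but are not supported:

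- *The primary baseline is compromised.* It is not. {13} and {18a} both place primary outcomes on the pre-allocation form, and {16a} needs PHQ-8 and GAD-7 for stratification. The wording in {18a} about primary outcomes in the second battery may be a drafting slip, and the schedule figure, not shown here, may settle it. The two texts still conflict.
- *Each student answers to the leader of the assigned arm.* {18a} says only that supervised lay providers hand out the forms. That it is the group's own leader is an inference from {16c}.
- *Attention checks exclude students after allocation.* Eligibility criteria {10} says "Participants who fail attention checks during baseline measures will be excluded". As an eligibility rule, this most naturally means screening on the first form. It would help to say so.
- *A 17 to 50% distortion of the time × condition estimate in general.* That range belongs to the gain score, or to an early slope for a measure skipped at the midpoint. For a measure taken at every visit the slope is distorted less.

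It can also be argued that completing baseline in {20a} means the first form only. Read alone, it could. The first-session exception in {18b}, justified by essential baseline data, points the other way, and nothing in the article resolves it.

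**Conclusion.** The point holds in this form. Some secondary-outcome baselines are collected after allocation under unblinded conditions, contrary to the order implied by {16a}. {13} and {18a} contradict each other on the content of the two forms. {18b} with {20a} allows randomised students to be removed for an event after allocation while the set is called intent-to-treat. The removal problem affects all outcomes; the baseline-shift problem concerns the secondary outcomes and the mediators drawn from them.

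Neither size can be derived from the document. On the assumed shift of 0.05 to 0.15 SD, the distortion relative to 0.3 SD is 17 to 50% for a gain score, 13 to 40% for a linear slope to the 1-month follow-up, and 7 to 21% over the full follow-up, the last two for a measure taken at every visit. On the assumed unequal removals, the contrast moves by 0.015 to 0.05 SD. Equal removal of students who differ from the rest to the same degree in each arm would leave the contrast unbiased. These effects may be modest, but they are avoidable.

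**What to change.** 1. Collect the second battery before group assignments are disclosed, either at the consent sitting or before the allocation list is announced.
2. Name the consent-visit form as the only baseline for PHQ-8, GAD-7 and SWEMWBS.
3. State that the attention-check exclusion in {10} applies only to that pre-allocation form.
4. Define the intent-to-treat set as everyone randomised except those who withdraw consent. Impute missing secondary baselines as {20c} already provides, and collect grades for first-session absentees as well.
5. Reconcile {13}, {16a}, {18a}, {18b} and {20a} so that they give one order of events, one list of measures per form and one analysis set.

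The cost is a longer consent sitting, or a slightly later announcement of groups.

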**Fig. 1. Fig1:**
[figure not shown]
Schedule of enrollment, interventions, and assessments for the five-arm Shamiri intervention trial. *Note that academic outcomes will be collected as they become available, with the likely timeline being pre-intervention academic outcomes collected in May–June 2021, mid-intervention academic outcomes being collected in August–September 2021, and post-intervention academic outcomes being collected in December 2021–January 2022

### Sample size {14}

We conducted a power analysis using Optimal Design, a statistical simulation software which can estimate sample size for randomized controlled trials assessed using multi-level (i.e., mixed effects) models [74]. In Optimal Design, we estimated the required sample size for a person-randomized trial with six-time repeated measures (baseline, midpoint, post, 1-month follow-up, 3-month follow-up, 6-month follow-up, and 9-month follow-up). Additionally, for each outcome measure, we have four contrasts of primary interest (each intervention condition compared to the control), thus, using a conservative *p* value correction, we would divide the typical alpha value of .05 by four and get a *p* value threshold for significance of .0125. Finally, we assumed that we are interested in detecting a minimum post-treatment effect size of .3. We selected this value for the following reasons: 1) it is slightly lower than the effect sizes found in most previous trials of Shamiri, which range from .32–.83 at the latest follow-up points [3, 20, 33, 34], which will allow us to detect potentially smaller effects of the individual component interventions, and to detect effects in a universal sample, and 2) a standardized effects size of .3, which is considered small to medium, remains clinically meaningful and important in our view, whereas a change smaller than that may not be as clinically meaningful. Given these parameters, we found that a sample of 515 students would be needed to conduct a two-group trial with a power of .80. So, for this five-group trial, we multiplied that by 2.5, to get a final target sample size of 1288 students. Because in a past trial with 7-month follow-up there was a high dropout rate during follow-up of up to 40% [33], we will initially invite 2147 students to the sessions, assuming that around 40% of them will drop out prior to the sessions or during the follow-up period.

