### Trial design {8}

This study is a parallel-group randomized controlled comparative effectiveness trial with five arms:1) the Combined Shamiri Intervention (consisting of a growth element, a gratitude element, and a value affirmation element; henceforth called “Shamiri”), 2) the Growth Intervention, which encompasses content related to growth mindset and strategies for growth, 3) the Gratitude Intervention, which incorporates content to build feelings of gratitude and expression of gratitude, 4) the value affirmation intervention, which incorporates content to help students identify and better act on their personal values and sense of purpose, and 5) a study skills control group, an active control group teaching students study skills that may be useful to them as students. Each condition is described further below under “interventions.” Participants will be allocated within each school to the five conditions with a 1:1:1:1:1 ratio, or equal probability for assignment to each condition. Each arm will require 4-h-long sessions spanning 4 weeks and will be delivered in a group (8–15 students) setting by a local, trained lay provider between the ages of 18 and 24. Measures of mental health, wellbeing, and character strengths will be collected at baseline, 2-week midpoint, 4-week endpoint, and 1-month, 3-month, 6-month, and 9-month follow-up. Academic data will be collected for the school terms before, during, and after the intervention. De-identified trial data will be available in an online repository and upon request.

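### The stated power of .80 has no term for treatment group or lay provider, and no figure is given for grades, which have only three term values

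*Protocol article*

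**What the plan says.** The Sample size section {14} describes its model thus: "we estimated the required sample size for a person-randomized trial with six-time repeated measures". The occasions it then lists number seven: "baseline, midpoint, post, 1-month follow-up, 3-month follow-up, 6-month follow-up, and 9-month follow-up". The inputs are a standardized effect of .3, power of .80 and a "value threshold for significance of .0125", which is .05 divided by the four contrasts with control. The result is that "we found that a sample of 515 students would be needed to conduct a two-group trial with a power of .80". Multiplying by 2.5 gives 1288, and allowing for 40% loss gives 2147 invited. The section states no ICC, group size or design effect.

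Each arm, control included, "will be delivered in a group (8–15 students) setting by a local, trained lay provider" (Trial design {8}). The section on statistical methods for primary and secondary outcomes {20a} starts from a participant random intercept. It adds, as structures to be tested and possibly dropped, "random effects for groups within group leaders" and terms for school.

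Academic performance is one of four primary outcomes. For it, "Academic data will be collected for the school terms before, during, and after the intervention" (Trial design {8}), so each student has three values.

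**The concern.** Students are randomized individually, so groups should not differ systematically at baseline. Four weeks of shared sessions under one leader can still make the outcomes of group members alike. A calculation that treats students as independent then overstates the information in 515 students. The protocol is aware of the issue: its background section {6a} says an earlier microtrial was underpowered for small effects because it was cluster-randomized, and presents this trial as well powered.

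Grades raise a second question. The only calculation shown rests on the questionnaire schedule, and three values estimate a time trend less precisely than seven.

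The trial is meant to show which elements deserve dissemination, and the Sample size section treats effects below .3 as possibly not clinically meaningful. If .80 is taken at face value, a null contrast for a single-element arm could be read as evidence against an effect of .3 when the chance of detecting it was appreciably lower.

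**Working it through.** **Inputs from the protocol:** effect d = .3, alpha = .0125 (two-sided assumed), N = 515 per contrast, groups of 8–15, seven listed questionnaire occasions, three grade terms. **Assumed, because the protocol gives none:** group ICC of .01 to .05, the ratio r of residual to slope variance, and unit-spaced occasions.

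**1. Reproducing 515 with independent students.**
- Single-time-point comparison: N = 4(2.498 + .842)²/.3² = 496. Power at 515 is Φ(.3√515/2 − 2.498) = Φ(.906) = .82.
- Linear-growth comparison: noncentrality λ = (N d²/4) × 1/(1 + r/SS), where SS is the sum of squared deviations of the occasion times: 28 for seven occasions, 17.5 for six, 2 for three. With r = 1, seven occasions need 517 (power at 515 is .80) and six need 528 (power .79). With r about .56, six occasions need 515.

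So the figure reproduces without any cluster term, and it does not tell six occasions from seven. The later steps also reproduce: 515 × 2.5 = 1287.5, and 1288/.6 = 2147.

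**2. Adding group clustering.** Divide λ by DE = 1 + (m − 1) × ICC. With seven occasions and r = 1, λ before clustering is 515 × .09/4 × .9655 = 11.19. For m = 15 and ICC = .05, DE = 1.70, λ = 6.58 and Φ(√6.58 − 2.498) = .53; the F distribution gives .52. The detectable effect is about .30 × √DE.

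| ICC (assumed) | DE, m = 8 to 15 | Power for .3 | Detectable effect |
|---|---|---|---|
| .01 | 1.07 to 1.14 | .77 to .73 | .31 to .32 |
| .02 | 1.14 to 1.28 | .73 to .67 | .32 to .34 |
| .05 | 1.35 to 1.70 | .65 to .52 | .35 to .39 |

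Power drops below .78 at an ICC of about .006 (m = 8) or .003 (m = 15). If 40% loss thins a mid-range group of 11.5 to 6.9 analysed, DE is 1.059, 1.118 and 1.295. Power is then .77, .75 and .67 at the three ICCs.

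**3. Grades with three values, no clustering.** SS = 2, so the factor 1/(1 + r/SS) is 1/(1 + r/2). With r = 1, λ = 11.59 × .667 = 7.73 and power at 515 is .61; 747 per contrast would be needed for .80. The ratio is not known. Values of r from .2 to 1.6 all bring the seven-occasion N within 3% of 515, and over that range grades power runs from .77 to .51. At r = 1, clustering with ICC .01 to .05 and m of 8 to 15 lowers it to between .57 and .36.

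**4. Grades of leavers.** The retention section {18b} keeps grades for students who leave after the first session. If all 2147 invited were randomized and had grades, a contrast would have 2147 × 2/5 = 859 students. Three-term power at r = 1 would then be .86 without clustering, and about .78 at ICC .02 with m = 11.5.

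**The case against.** Several points on the other side have force.

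- **Holm.** The analysis uses Holm-Bonferroni, not a fixed .0125. If all four arms truly have an effect of .3, average power per contrast with groups of 11.5 is about .83 to .85, .79 to .81 and .67 to .69 at ICC .01, .02 and .05; the two ends are the growth and single-time-point models. With one effective arm it is only about .75 to .77, .70 to .72 and .58 to .61. Holm therefore helps most when every arm works, and that is what the trial is asking.
- **Analysed N.** 1288 is the number expected after loss, and the analysis keeps everyone randomized with baseline data, using imputation. Early measures from later dropouts add information, by an amount that cannot be computed here.
- **Design effect.** The formula suits a single-time mean, while the test is of time × condition, so the ICC of change is the relevant one. Leaders are trained in every arm and assigned at random; if one leader runs groups in several arms, leader effects partly cancel.
- **Reading of .3.** If .3 is a difference at one time point, the number of occasions drops out and only clustering matters. The section specifies repeated measures, however, and the planned test is of trajectories.

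Some stronger readings are tempting but unsupported. A reader might infer that the protocol expressly applies the seven-occasion calculation to grades; its remark about each outcome measure concerns dividing alpha, not the number of occasions. One might take 515 as proof that seven occasions were used; six fit equally well. One might quote .61 as the grades power; that is one point in a range, and it ignores leavers' grades. Nor is this a cluster-randomized trial or an arithmetic slip: the sums are right for the model used. The protocol itself does not say that a null result would rule out .3.

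**Conclusion.** The concern holds in a limited form. The stated .80 at 515 per contrast and alpha .0125 requires a group ICC close to zero, an assumption the protocol neither states nor defends while its own analysis section recognises group and leader levels. For ICCs of .01 to .05 and groups of 8 to 15, power is about .77 to .52. These figures are conditional on assumed ICCs and a simple design effect, so they do not show that the trial is underpowered. They show that .80 is the favourable end.

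For grades, no calculation matches the three-term schedule. Power at 515 is about .77 to .51 before clustering, depending on an unknown variance ratio, and could exceed .80 if enough leavers' grades are counted. The mismatch between six and seven occasions is a plain inconsistency with little effect on N (528 against 517 at r = 1).

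**What to change.** Keep N and rewrite the Sample size paragraph:

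1. Restate power and detectable effect with DE = 1 + (m − 1) × ICC over a stated ICC range. Use the ICC of the tested change and the group size expected in the analysis. Say whether the figure is for fixed .0125 or for Holm, and under how many effective arms.
2. Give a separate figure for academic performance, with three measures, its own variance assumptions and the N expected once leavers' grades are included.
3. Reconcile the stated six occasions with the seven listed, and report the variance components behind 515.

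The cost is a rewritten paragraph with less favourable figures; no extra participants are needed.
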